## Abstract

**Background:**

Tinnitus is the perception of a sound in the absence of an objective physical source. Up to now, there is no generally accepted view how these phantom sounds come about, and also no efficient treatment. Patients are turning to complementary or alternative medical therapies, such as acupuncture. Based on the theory of traditional Chinese medicine, acupoints located on both the adjacent and distal area of the disease can be needled to treat disease. Furthermore, the way of combining acupoints is for strengthening the curative effect. We aim to evaluate the efficacy of acupuncture at local points in combination with distal points in subjective tinnitus patients.

**Method:**

This trial is a randomized, single-blind, controlled study. A total of 112 participants will be randomly assigned to one of four treatment groups receiving acupuncture treatment for 4 weeks. The primary outcome measure is subjective tinnitus loudness and annoyance perception, which is graded using the Visual Analogue Scale (VAS). The assessment is at baseline (before treatment initiation), 4 weeks after the first acupuncture session, and 8 weeks after the first acupuncture session.

**Discussion:**

Completion of this trial will help to identify whether acupuncture at local acupoints in combination with distal acupoints may be more effective than needling points separately.

**Trial registration:**

International Standard Randomized Controlled Trial Number Register: ISRCTN29230777

## Background

### Tinnitus

Subjective tinnitus is a frequent auditory sensation (for example, a tone, hissing, or buzzing sound, and sometimes combinations of such perceptions) experienced in the absence of an external or internal acoustic stimulus. An estimated prevalence in the adult population across studies is about 10% to 15% [1-3], where 1% to 3% of the population has severe, distressing tinnitus. Among severe sufferers, tinnitus causes disability associated with concentration deficits, hypersensitivity to sounds, anxiety, depression, irritability, agitation, and insomnia. Often a combination of several complaints could disrupt daily activities and has a negative impact on quality of life. It represents a worldwide major healthcare problem with an enormous social and economic demand for therapeutic treatment [4,5]. Pharmacotherapy (antidepressants, benzodiazepines), cognitive therapies, or electronic devices that try to cancel the tinnitus have all been tried either separately or in combination but the success rate is not high. Attempts to develop evidence-based therapies have been thwarted by a poor understanding of the pathophysiology [6,7]. Increasingly, patients are turning to complementary and alternative medical therapies. Acupuncture is among the most popular.

### Acupuncture

Acupuncture has been used to treat tinnitus for a long time. Neuroscience studies related the effects of acupuncture to neuronal stimulus, activation of endogenous opioid mechanisms and neuropeptides which stimulate specific brain structures [8]. It has been reported that acupuncture can yield immediate relief, both from the loudness and the disturbing quality of tinnitus, significant improvement in quality of life, less tension, and better sleep [9-12]. In contrast, an analysis of six randomized clinical trials of acupuncture for tinnitus failed to demonstrate any efficacy [13]. Based on the theory of traditional Chinese medicine (TCM), acupoints located on both the adjacent and distal area of the disease can be needled to treat disease. Furthermore, the way of combining these acupoints is often used for strengthening the curative effect.

### Aims

The aim of our study is to evaluate the efficacy of acupuncture at local points in combination with distal points in subjective tinnitus patients.

## Methods

We perform the study according to common guidelines for clinical trials (Declaration of Helsinki, International Conference on Harmonisation (ICH)/WHO Good Clinical Practice standards (GCP) including certification by an external audit). The trial protocol has been approved by the Research Ethical Committee of Beijing Hospital of Traditional Chinese Medicine Affiliated to Capital Medical University. This trial was registered with ISR CTN at Current Controlled Trials (ISRCTN29230777).

### Population

Patients will be recruited in acupuncture clinic, Beijing Hospital of Traditional Chinese Medicine affiliated to Capital Medical University with a target sample size of 112 subjects. The trial is executed from February 2012 to December 2014.

### Inclusion criteria

Patients who require for all of the following conditions will be considered for enrollment:

1. Diagnosis of subjective tinnitus, unilateral or bilateral

2. Age 18 to 65 years, either sex

3. Tinnitus duration of at least 3 months

4. Not to receive another treatment during the clinical trial period

5. Written and informed consent

### Exclusion criteria

1. Objective tinnitus (objective tinnitus is audible to the examining/auscultating physician, whereas subjective tinnitus can only be perceived by the patient)

2. Underlying disease or history:

2.1. Cerebral vascular events

2.2. Neurodegenerative disorders

2.3. Otitis media

2.4. Acoustic tumor

2.5. Prior brain surgery

2.6. Inner ear malformation

2.7. Head trauma

2.8. Ototoxic drug medication

3. Women in pregnancy and lactation or without contraception

4. Inability to correct use of test equipment: unable to cooperate during audiologic examination

5. Patients who cannot communicate reliably with the investigator or who are not likely to cope with the requirements of the trial

### Interventions

This trial is a randomized, single-blind, controlled study. Participants will receive acupuncture for 4 weeks. All candidates go through a standardized interview and receive more information about the study and the treatments. They also undergo audiological testing of hearing thresholds, minimal masking levels, and loudness discomfort levels carried out by an audiologist in Tongren Hospital affiliated to Capital Medical University.

Time points are as follows (Figure 1):

Visit 1: screening

Visit 2: treatment initiation, participants will receive acupuncture for 4 weeks

Visit 3: 4 weeks after first acupuncture, follow-up and treatment finish

Visit 4: 8 weeks after first acupuncture, follow-up

**Figure 1 F1:**
[figure not shown]
Flowchart.

Patients who meet the inclusion criteria and none of the exclusion criteria are randomized to one of four treatment groups: group A will receive acupuncture at local acupoints in combination with distal acupoints; group B will receive acupuncture at local acupoints in combination with distal non-acupoints; group C will receive acupuncture at local non-acupoints in combination with distal acupoints; group D will receive acupuncture at local non-acupoints in combination with distal non-acupoints. Acupuncture points selected as follows (Figure 2):

 Local acupoints: Baihui (GV 20), Shenting (GV 24), Yifeng (TE 17), Tinghui(GB 2), Ermen (TE 21)

 Distal acupoints: Waiguan (TE 5), Zhongzhu (TE 3), Qiuxu (GB 40), Zulinqi (GB 41)

 Distal non-acupoints

Distal non-acupoint I: the radial side of forearm, the ulner side of the middle of the line joining Shaohai (HT 3) and Shenmen (HT 7), between heart meridian of hand-shaoyin and small intestine meridian of hand-taiyang

Distal non-acupoint II: the radial side of forearm, the junction of the upper 1/4 and lower 3/4 of the line joining HT 3 and HT 7, between heart meridian of hand-shaoyin and small intestine meridian of hand-taiyang

Distal non-acupoint III: lateral side of lower leg, 3 cun above the tip of external malleolus, 1.5 cun behind anterior crest of the tibia, between the stomach meridian of foot-yangming and gall bladder meridian of foot-shaoyang

Distal non-acupoint IV: lateral to the shank, 3 cun below Yanglingquan (GB34), the midway between gall bladder meridian of foot-shaoyang and bladder meridian of foot-taiyang

 Local non-acupoints

Local non-acupoint I: one finger-breadth (middle finger) inferior to Daying (ST5) in the body of mandible

Local non-acupoint II: midpoint between Yangbai (GB14) and the midline of the head, between governor meridian and gall bladder meridian of foot-shaoyang

Local non-acupoint III: high spot of the angle of mandible

Local non-aupoint IV: on zygomatic arch, the midway between ST 7 and GB 3

**Figure 2 F2:**
[figure not shown]
The points used in the trial.

Acupuncture will be performed with sterile needles by one therapist with more than 22 years of experience and an acupuncture license from the Chinese medicine practitioner license from the Ministry of Health of the People’s Republic of China. Treatment will be conducted over a period of 4 weeks, at a frequency of two sessions per week. No additional treatment is allowed.

### Randomization and blinding

A research coordinator screen and enroll participants at clinic. After participants completed a baseline evaluation, another research coordinator who is uninvolved with data collection randomly assigns them to one of four treatment groups by using a computer-generated, blocked random-allocation sequence. The random list is generated with SAS software (SAS Institute, Inc., Cary, NC, USA). This research coordinator informs the acupuncturist of the treatment assignment.

The patients, data collection staff, and data analysts are blinded during the study period. The acupuncturist is not blinded to the treatments they delivered because acupuncture manipulation makes it impossible. During the intervention, acupuncturist and the personnel who collect data are segregated immediately after the treatment start and are instructed not to exchange information with each other.

### Primary outcome measures

Subjective tinnitus loudness and annoyance perception is graded using the VAS. The assessment is at baseline (before treatment initiation), 4 weeks after the first acupuncture session, and 8 weeks after the first acupuncture session.

### Secondary outcome measures

 Change of tinnitus severity according to the tinnitusquestionnaire of Tinnitus Handicap Inventory (THI):

1.1. F: Functional subscale (11 factors)

1.2. E: Emotional subscale (9 factors)

1.3. C: Catastrophic subscale (5 factors)

 Changes of tone and noise parameters of tinnitus are assessed by tinnitus matching (screening *versus* week 8).

 Perceived credibility of acupuncture would be evaluated by the Treatment Credibility Scale (TCS) after a 4-week acupuncture session. It is a five-item questionnaire ranging from 1 (not at all) to 5 (very confident); items are averaged to provide a single treatment credibility score, with high scores reflecting high treatment credibility.

 To evaluate the adequacy of blinding, we will ask participants to rate how certain they are that they have received traditional acupuncture or new method of acupuncture on a seven-point scale (1 very sure, 7 very uncertain) after 4 weeks of treatment.

Each question of the THI can be answered by the patient with either ‘often’ (4 points), ‘sometimes’ (2 points), or ‘never’ (0 points) with a maximum total score of 100 points indicating most severe suffering from tinnitus. The assessment is at baseline (before treatment initiation), 4 weeks after the first acupuncture, and 8 weeks after the first acupuncture.

Participants should report the adverse events they experienced, including discomfort or bruising at the sites of needle insertion, nausea, or feeling faint after each treatment.

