### Statistical methods

The trial aims to detect a difference in loudness and annoyance perception of tinnitus between the four study groups. This is deemed a clinically significant difference of average 20-point reduction on the VAS scores of loudness in acupuncture group when comparing with the sham-control group based on previously published studies [14]. The standard deviation is 25.9 in acupuncture group and 23.8 in the sham-control group, respectively, as previous studies have suggested [15].

The following formula was used for a four-group trial [16]:

(1)$$n1=n2=2{\left[\frac{\left(\mathrm{u\alpha}+\mathrm{u\beta}\right)s}{\delta }\right]}^{2}$$

Calculations are performed using 80% power, a 5% significance level (two-side). The required sample size is approximately 24 participants for each group. We plan to enroll a total of 112 participants with 28 in each group, allowing for a 25% withdrawal rate.

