## Discussion

We have presented the design and the protocol for the randomized controlled trial of acupuncture at local and distant points for subjective tinnitus. Completion of this trial will help to identify whether acupuncture at local acupoints in combination with distal acupoints may be more effective than needling points separately.

It is hoped that this study will encourage renewed interest in acupuncture’s potential for treating people with tinnitus. Recent researches have created a climate where acupuncture might be assumed to be ineffective [17]. However, there is as yet inadequate evidence on which to base a judgment on acupuncture’s effectiveness for tinnitus. Well-designed randomized controlled trials where patients are representative of people with tinnitus in the general population are needed.

In this study, the side-effects of acupuncture will be reported by patients. Several large surveys have also provided evidence that acupuncture is a relatively safe treatment [18]. The results could also provide consumers with information about viable choices. If acupuncture is demonstrated to be effective and safety in tinnitus, there may be a number of patients with these conditions who seek out acupuncture rather than pharmacotherapy.

Patients are informed in a manner suggesting that two different types of acupuncture treatment were compared. One type is traditional, another is new, and the effect of both is uncertain, not mentioning terms such as ‘placebo’ or ‘sham’. Similar strategies of informed consent have been used in most previous acupuncture trials [19].

However, our study has several limitations. Deciding on an appropriate control procedure for clinical studies on acupuncture is a particular challenge [20]. Previous randomized, controlled trials of acupuncture suggest that needling of acupoints is as effective as non-points, in particular for pain releif, although both interventions were more effective than a waiting list control [21-23]. Few guidelines exist, however, for identifying appropriate sham point locations; the depth, direction, and duration of needle insertion; or the need for needle stimulation. In the present study, physicians were instructed to avoid manual stimulation of the needles and provocation of Deqi at non-acupuncture points. However, we cannot rule out that this intervention may have some physiological effects.

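### The blinding item records how sure patients are but not which method they believe they had, so confident correct and confident wrong beliefs score the same

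*Protocol article*

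**What the plan says.** The Protocol article describes the item under Secondary outcome measures. Its purpose is explicit: "To evaluate the adequacy of blinding, we will ask participants to rate". What they rate is "how certain they are that they have received traditional acupuncture or new method of acupuncture on a seven-point scale", and the anchors and timing are "1 very sure, 7 very uncertain) after 4 weeks of treatment". One scale is described. No question about the believed method is mentioned.

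The surrounding text sets the context:

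- Randomization and blinding: "The patients, data collection staff, and data analysts are blinded during the study period". The acupuncturist is not blinded.
- Primary outcome measures: loudness and annoyance are graded by VAS at baseline and at "4 weeks after the first acupuncture session, and 8 weeks after the first acupuncture session".
- Discussion: "Patients are informed in a manner suggesting that two different types of acupuncture treatment were compared". One type is presented as traditional and the other as new.
- Interventions: there are four arms. A has true points at both sites, B only locally, C only distally, and D at neither.
- Secondary outcome measures also lists a separate credibility measure: "Perceived credibility of acupuncture would be evaluated by the Treatment Credibility Scale (TCS) after a 4-week acupuncture session".

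**The concern.** Whether blinding held is judged by setting what patients believe they received against what they did receive. That needs the direction of the belief. A scale running from sure to uncertain gives only its strength. Two group D patients, one convinced of the traditional method and one convinced of the new one, both score 1, although only the second may have seen through the allocation.

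The check carries weight in this trial. The primary outcome is the patient's own rating, and the person delivering treatment knows the arm. The Discussion also says that manual stimulation and Deqi are avoided at the non-acupoints, which is a difference patients might feel. This item is the only direct check on patient blinding that the article describes; the credibility scale asks something else. If many patients turn out to be sure, the trial would have no data to show whether they were right, and a belief that was never recorded cannot be recovered in the analysis.

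**Working it through.** The plan gives no figure for this item, so there is none to reproduce. The check is a reading of the item followed by an illustration.

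**Step 1. Can the printed scale carry direction?** A two-ended scale would have *sure of traditional* at one end and *sure of new* at the other. The printed ends are very sure and very uncertain, which rules that out. Two ratings, one per method, would recover direction, but the text describes a single seven-point scale. Followed as written, the item yields strength of belief only.

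**Step 2. Extreme case.** Take traditional as the answer matching group A and new as the answer matching group D. The article does not state this matching; it is an assumption.

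| Situation | Mean rating, A | Mean rating, D | Blinding |
|---|---|---|---|
| All sure, all right | 1 | 1 | lost |
| All sure, all say traditional | 1 | 1 | belief unrelated to arm |

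The ratings are identical and the conclusions opposite.

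**Step 3. A less extreme case, using the Bang index for one arm.** Inputs: n = 28 per arm (Statistical methods). Assumed: s = 20 patients sure and 8 uncertain, with the uncertain ones counted as having no guess. Let c be the number of sure patients who are right. Then

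BI = (2c/s - 1) × s/n = (2c - s)/n.

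- c = 20 (all right): (40 - 20)/28 = +0.71
- c = 10 (half right): (20 - 20)/28 = 0.00
- c = 0 (all wrong): (0 - 20)/28 = -0.71

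The certainty ratings are the same in all three rows.

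**Step 4. Dependence on the assumed split.** With c free to run from 0 to s, the index can lie anywhere between -s/n and +s/n:

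| Sure, of 28 | Range of index |
|---|---|
| 0 | 0 |
| 4 | -0.14 to +0.14 |
| 10 | -0.36 to +0.36 |
| 20 | -0.71 to +0.71 |
| 28 | -1.00 to +1.00 |

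The item is therefore informative when few are sure, and loses its value as the share of sure patients grows.

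**Step 5. Two labels, four arms.** Patients know of two methods. Groups B and C each combine true points at one site with non-acupoints at the other, so the article's wording does not define a correct answer for them. Once guesses are collected, these two arms cannot simply be pooled with A or D.

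**The case against.** The strongest reply is that an article condenses. A patient can hardly rate certainty about one of two named methods without having one in mind, so the actual form may record the choice as well. That is possible, and if so one clarifying sentence settles the point. But the article gives purpose, content, scale and anchors, and an item applied exactly as given does not do what it is said to do. This is more than an omitted detail.

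The second reply stands: the item is not worthless. If most patients rate near 7, that is evidence that blinding held, and differences in certainty between arms also carry some information. A reader might infer that the item can say nothing about blinding; the text does not support that.

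A reader might also infer that asking at week 4, once patients have felt any benefit, makes blinding unassessable. It does not. Belief and response may be hard to separate by then, but assessing at the end of treatment is a defensible choice, and the week-8 VAS is still to come. Nor is the credibility scale at fault: it is presented as a separate measure of credibility and is not offered as a test of allocation guesses.

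Asking in terms of two methods is also reasonable, since it matches what patients were told and does not reveal the four-arm design. Finally, the item is a secondary check, and the Discussion already concedes that bias from unblinding cannot be excluded. That limits the consequence but does not make the check work.

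**Conclusion.** The point holds in a limited form. As described, the item measures strength of belief without its direction. It can support blinding if patients are mostly uncertain, but it cannot tell correct from incorrect beliefs once a material share are sure. Under the assumed split of 20 sure and 8 unsure, the ambiguity in the Bang index is ±0.71; in general it is plus or minus the proportion who are sure.

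The conclusion rests on the item being used as printed, with no separate record of the believed method. It changes no primary estimate, test or sample size. It should be corrected because patient blinding is a main safeguard for a patient-rated outcome here, and the correction is small.

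**What to change.** At the existing week-4 assessment, first ask which method the patient thinks was received (traditional, new, or do not know), then take the certainty rating as planned. If the form already does this, say so in the protocol.

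Report the distribution of guesses, or a blinding index, for each of the four arms. Show B and C separately, because each mixes acupoints and non-acupoints. If an index is used, state beforehand which answer counts as matching the allocation in each arm.

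The cost is one extra question. According to Trial status, recruitment was still under way, so later patients can be covered; those who have already completed week 4 will lack the answer, and their number should be reported.

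An additional early measurement is optional. It could help separate belief from response, but it would fall at a treatment session outside the four listed visits, would have to respect the separation of acupuncturist and data collectors, and might itself prompt patients to wonder about their allocation.

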### Statistical methods

The trial aims to detect a difference in loudness and annoyance perception of tinnitus between the four study groups. This is deemed a clinically significant difference of average 20-point reduction on the VAS scores of loudness in acupuncture group when comparing with the sham-control group based on previously published studies [14]. The standard deviation is 25.9 in acupuncture group and 23.8 in the sham-control group, respectively, as previous studies have suggested [15].

The following formula was used for a four-group trial [16]:

(1)$$n1=n2=2{\left[\frac{\left(\mathrm{u\alpha}+\mathrm{u\beta}\right)s}{\delta }\right]}^{2}$$

Calculations are performed using 80% power, a 5% significance level (two-side). The required sample size is approximately 24 participants for each group. We plan to enroll a total of 112 participants with 28 in each group, allowing for a 25% withdrawal rate.

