### Data analysis

Data will be analyzed according to the 2×2 randomized factorial study designs. The statistical model includes two fixed factors (both local acupoints and distal acupoints). Interaction is evaluated using the interaction term in the ANOVA model and by visual assessment of profile plots. As no interaction between local acupoints and distal acupoints is detected, results are presented as a factorial design (for example, all patients receiving acupuncture at local acupoints in combination with distal non-acupoints; and all patients receiving acupuncture at local non-acupoints in combination with distal acupoints).

Data analysis will be conducted by statisticians who are independent from the research team. Every analysis is conducted using the SPSS software (SPSS 12.0 KO for Windows ©).

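### Enrolling 28 per group does not allow for 25% withdrawal: it leaves 21, not the required 24, and power falls to about 74%

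*Protocol article*

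**What the plan says.** All the relevant figures stand in one section of the protocol article, Statistical methods.

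- Error rates: "Calculations are performed using 80% power, a 5% significance level (two-side").
- Target difference: a "clinically significant difference of average 20-point reduction on the VAS scores of loudness in acupuncture group" compared with sham control.
- Variability: "The standard deviation is 25.9 in acupuncture group and 23.8 in the sham-control group".
- Result of the formula: "The required sample size is approximately 24 participants for each group".
- Enrolment: "We plan to enroll a total of 112 participants with 28 in each group, allowing for a 25% withdrawal rate".

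No other section gives a different withdrawal rate, and none says that the 24 already includes an allowance for withdrawal. The Data analysis section adds the design context: "Data will be analyzed according to the 2×2 randomized factorial study designs".

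**The concern.** Two consecutive sentences give three figures (24 needed, 28 enrolled, 25% lost), and any two of them contradict the third. The allowance for withdrawal exists so that the required number is still there at the end of the trial. Here, if the anticipated withdrawal occurs, it is not.

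The sample size statement is what readers use to judge a non-significant result. Someone who takes it at face value will believe that the trial keeps 80% power for a 20-point difference with a quarter of the patients gone. On the basis on which the plan calculated that power, this is not so.

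**Working it through.** **Inputs**, all from Statistical methods: δ = 20 VAS points; standard deviations 25.9 and 23.8; two-sided α = 0.05 (z = 1.96); power 80% (z = 0.842); 24 required per group; 28 enrolled per group, 112 in total; withdrawal 25%.

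**Step 1. Reproduce the 24.** The plan does not say how it combines the two standard deviations, so I take the root mean square:

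s = √[(25.9² + 23.8²)/2] = 24.87

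The printed formula then gives

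n = 2[(1.96 + 0.842) × 24.87/20]² = 24.3 per group.

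The stated figure of about 24 is reproduced. It is the number before any allowance for withdrawal. Strict rounding up gives 25. Using 25.9 alone gives 27, and 23.8 alone gives 23.

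**Step 2. Try to reproduce the 28 from 24 and 25%.**

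| Method | Per group | Total |
|---|---|---|
| Divide by the retained fraction: 24/0.75 | 32 | 128 |
| Common shortcut: 24 × 1.25 | 30 | 120 |
| Plan | 28 | 112 |

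Neither method gives 28. Starting from 25 widens the gap: 25/0.75 = 33.3, so 34 per group and 136 in total.

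**Step 3. Work backwards from 28.**

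- Completers at 25% loss: 28 × 0.75 = 21 per group, 84 in total.
- Loss that still leaves 24: 1 − 24/28 = 14.3%.

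**Step 4. Power for a comparison of two groups.** With the normal approximation behind the plan's formula,

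power = Φ(δ/[s√(2/n)] − 1.96).

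For n = 21: s√(2/21) = 7.68, 20/7.68 = 2.61, and Φ(0.65) = 74.1%.

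| Completers per group | Normal approximation | t test |
|---|---|---|
| 24 (requirement) | 79.6% | 77.9% |
| 21 (28 less 25%) | 74.1% | 72.0% |
| Loss, in percentage points | 5.5 | 5.9 |

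The choice of standard deviation does not rescue the claim. With 21 per group and the normal approximation, power is 70.6% for a standard deviation of 25.9 and 77.7% for 23.8. Both are below 80%.

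**The case against.** The arithmetic is hard to dispute. What can be argued is which figure is wrong, and how much it matters.

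**The percentage may be a misprint.** A 15% allowance leads almost exactly to 28: 24/0.85 = 28.2 and 24 × 1.15 = 27.6. If 15% was meant, the enrolment is about right and only the rate is wrong. This is possible, but nothing in the article confirms it. It bears on which correction the sponsor should choose, not on whether one is needed.

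**The planned analysis is factorial.** A main effect compares two pooled groups with the other two, so 25% withdrawal leaves 42 against 42. If a factor's main effect were 20 points with the same standard deviation, power would be about 96%. That is correct on its assumption, which the plan does not make: its 20 points is acupuncture against sham, and its requirement is set for each group. If instead 20 points is the gap between group A (both true point sets) and group D (neither), shared equally by two additive factors, each main effect is 10 points and its power is about 45%. The trial's question, whether the combination beats needling either set separately, also turns on single-group contrasts or on the interaction. For an assumed interaction of 20 points, power is about 50% with 24 per group and 45% with 21.

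**Comparing 72% with 80% mixes methods.** This is fair. The 80% comes from a normal approximation, and by t test even 24 completers give only 77.9%. The loss due to withdrawal is therefore about 6 points, not 8.

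**The Discussion already calls the sample relatively small.** It does, but that does not tell readers that the withdrawal allowance is not met.

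**Conclusion.** The point holds: the sentence is wrong as written. With 24 required, 28 per group covers about 14% withdrawal. At 25%, 21 per group remain and power for a 20-point difference between two groups is about 74% by the plan's own formula (72% by t test), a like-for-like loss of about 6 percentage points.

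This rests on the plan's own figures, on pooling the two standard deviations, and on reading the 80% as a two-group comparison, which is how the formula and the per-group requirement present it. It does not show that every test in the factorial analysis is underpowered, nor which of the three figures the authors got wrong.

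**What to change.** Keep 112 patients and correct the enrolment sentence in one of two ways:

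1. State that 28 per group allows for about 14% withdrawal. This suits the case where 25% was a slip.
2. Keep 25%, and state that 21 per group then remain, with about 74% power for a 20-point difference between two groups by the formula used (about 72% by t test).

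Either costs one sentence and no extra patients; the price is a slightly less favourable figure.

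If the sponsor wants to keep both the 80% and the 25%, enrolment must rise to 32 per group, 128 in total, which is 16 more patients. The Trial status section says that recruitment is still under way, so that option is not closed by the text.
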